## Abstract

**Background:**

Hundreds of millions of children living in poverty worldwide are not reaching their full, developmental potential. Programs to promote nurturing and responsive caregiving, such as those in which community health workers (CHWs) conduct home visits to support optimal early childhood development (ECD), have been effective in small trials, but have not achieved similar success at scale. This study will explore two approaches to scale-up: converting a home-visiting model to a group-based model; and integrating the ECD curriculum into an existing government program. The objectives of the study are to: 1) Measure how the integration of ECD activities affects time and task allocation of CHWs and CHW psychosocial wellbeing; 2) Examine how the integration of ECD activities affects caregiver-child dyad participation in standard health and nutrition activities; and 3) Explore how the availability of age-appropriate play materials at home affects caregiver-child dyad participation rates in a group-based ECD program.

**Methods:**

We will randomize 75 communities in rural Madagascar into three arms: 1) [C], which is the status quo (community-based health and nutrition program); 2) [T], which is C + ECD group sessions [T]; and 3) [T +], which is T with the addition of an enhanced play materials package for home use. All children between 6–30 months old at the time of the intervention launch will be eligible to participate in group activities. The intervention will last 12 months and is comprised of fortnightly group sessions in which the CHWs provide caregiver-child dyads with information relating to ECD; CHWs will also include structured time for caregivers to practice the play and child stimulation activities they have learned. We will administer monthly surveys to measure CHW time use and task allocation, and we will leverage administrative data to measure caregiver-child dyad participation in the group sessions.

**Discussion:**

The results from the trial will provide the evidence base required to implement an integrated package of nutrition, health and ECD promotion activities at scale in Madagascar, and findings may be relevant in other low-income countries.

**Trial registration:**

This trial is registered on the AEA Social Science Registry (AEARCTR-0004704) on November 15, 2019 and on ClinicalTrials.gov (NCT05129696) on November 22, 2021.

## Background

Hundreds of millions of children around the world live in poverty, and as a result, are at risk of not reaching their developmental potential. Living in poverty increases exposure to multiple risk factors, such as poor nutrition, unstimulating home environments, inadequate water and sanitation, and environmental hazards, all of which can then lead to lower early childhood development (ECD) outcomes and educational attainment early in life, as well as worse labor market outcomes later in life [1–3]. Investments to promote developmental outcomes in early childhood – often in the form of parenting support/education and nutrition supplementation – can put children on a higher lifetime income trajectory, and can potentially crowd-out negative effects of early adverse events [1, 4]. A recent review of the effectiveness of parenting programs showed that, on average, participation in parenting programs resulted in improvements in child development outcomes [5]. Specifically, there were benefits for measures of cognitive development (standardized mean difference (SMD) 0.36, 95% CI 0·22–0·49, 19 studies), motor development (SMD 0.13, 95% CI 0·07–0·19, 9 studies), and socio-emotional development (standardized mean difference [SMD] 0·35, 95% CI 0·14–0·56, 13 studies). However, programs that have been effective in small program settings have not consistently achieved similar successes at scale.

A recent study in Madagascar (MAHAY) investigated the impact of an adaptation of a parenting program originating in Jamaica, the *Reach Up and Learn* program [6]. The program included fortnightly home visits by a dedicated community health worker (CHW) focusing on early childhood development (ECD) outcomes. Although the MAHAY program was carefully implemented and rigorously supervised, it failed to demonstrate significant effects on child outcomes. Researchers hypothesized that one of the reasons the intervention was not as effective as anticipated was that CHWs had to visit a large group of eligible children spread over a wide geographic area, resulting in long travel times and threats to personal safety. Another possible reason for the small effect sizes of the program on child development was the limited engagement by caregivers, possibly from lack of time or interest in topics covered. Furthermore, the caregivers may not have been able to act on suggestions made by CHWs because they did not have time or resources, or because they lacked materials, such as toys, and thus could not engage in the CHW suggestions regarding play.

A group adaptation of the previously tested MAHAY home visits was designed to address the issues that emerged in the MAHAY study. Over the course of a year, the adaptation of the group-based program was extensively pre-piloted in two communities. The revised, group-based program (MAHAY Mikolo, *“know how to take care”*) targets existing implementation issues that arose in the home-visit model by increasing coverage while reducing the amount of travel time spent by the CHWs given the greater efficiency possible with groups compared with one-on-one visits. The MAHAY Mikolo program incorporates behavioral nudges into the ECD group sessions to improve parental skills, promote peer support and encourage sustained caregiver-child play in between the fortnightly meetings. A subgroup of program communities will also receive boxes of age-appropriate toys and books to promote sustained play between group sessions and for daily practice at home. The group-based program has the potential to be integrated into Madagascar’s ongoing national reproductive, maternal and child health and nutrition program and rolled out gradually by the National Nutrition office (ONN) in Madagascar. Yet, there are important knowledge gaps about the potential costs or benefits of such an integration before scaling it up. A recent special issue in the Annals NY Academy of Science highlighted the importance of program implementation, and understanding issues such as fidelity, coverage, dosage, quality of delivery, and participants’ acceptance and enactment of program content, for program success [7]. The proposed evaluation builds from these lessons and assesses the feasibility of a group-based program by addressing key implementation research and policy questions.

The overall objective of the study is to examine the effects of integrating ECD group sessions into the existing, at-scale, community health and nutrition programs administered by the government in Madagascar by performing a process evaluation. The specific objectives of the study are to test how integrating ECD group activities affects the time and task allocation of CHWs and if adding these new activities may change the allocation of times towards health and nutrition activities, whether participation rates in health and nutrition activities are affected in communities where the ECD activities are offered, and if there is an additional benefit to providing age-appropriate toys and play materials for use at home on the take-up of ECD activities. To achieve these objectives, we will use a cluster randomized controlled trial design with three arms: a control group, with the status quo community-based health and nutrition program; a treatment arm with fortnightly group ECD sessions, based on Reach Up and Learn curriculum and supportive behavioral nudges, added to the status quo; and an enhanced treatment arm, where the intervention in the treatment arm is layered with the provision of individual toy boxes including age-appropriate toys. Detailed costing information on all activities using the ingredient methods will collected as part of the trial [8].

### Research questions

The primary questions we aim to address through this research are:

#### CHW time and task allocation

•Primary Question 1: How does the integration of ECD activities into existing health and nutrition responsibilities affect the time use and task allocation of CHWs?•Secondary Question 1: How does the integration of ECD activities affect measures of CHW psychosocial wellbeing?

The role of CHWs has expanded considerably over the past 50 years, particularly in low and middle income countries [9, 10]. CHWs are frontline workers tasked with bringing a wide variety of public health services to their communities, and crucially bridging the gap between remote communities and the formal health care system in a hub and spokes model. A large and growing body of evidence documents the positive effects of CHW-run programs on population health [9]. Understanding the impact of the demands of the CHW role on the health and wellbeing of the workers is an important dimension of research that has received limited attention.

CHWs are often time constrained, and thus it is crucial to understand how the addition of new ECD responsibilities will affect the time spent by CHWs on regular tasks relating to health and nutrition programming. There may be economies of scope through joint delivery. Specifically, by relying on an existing infrastructure and using the same CHWs, there may be substantial cost savings to having the two sets of program components delivered separately. On the other hand, these components may interfere or crowd each other out if the time, mental space and attention of the CHWs limits the implementation of multiple tasks. Crowd-out has been documented in the context of school meals and school-based nutrition interventions in other low- and middle-income country settings [11, 12].

The evidence on the positive effects of CHWs on health knowledge and outcomes in their target communities has been shown in a variety of contexts [9], but there has also been evidence of more troubling outcomes such as service delivery gaps [13, 14], infrequent home visits [15], and insufficient time spent on core health promotion activities [16, 17]. These intermediate outcomes that relate to how program demands impact the quality and composition of the time spent working by CHWs are crucial to measure how CHW programs impact downstream health knowledge and outcomes.

One important pathway that affects CHWs’ ability to effectively delivery primary health services to their communities is CHW workload. Existing literature on CHW time use has found evidence of workload strain. In one study in India, high administrative burdens resulted in CHWs spending time on administrative reporting tasks such as filling out paper registries instead of direct service provision [12]. Other papers in different settings have found that a source of strain for many CHWs is a lack of compensation commensurate with the demands of their jobs [18, 19]. This study will add to the evidence base of how increasing the scope of CHW workload affects their time and task allocation, not only on the different tasks that are related to the overall package of activities, but also the potential reallocation away from the CHW’s income generating activities or household caregiving or family chores.

Our secondary objective is to measure how expanding the CHW workload through the addition of ECD group sessions affects CHWs psychosocial wellbeing over the course of the program implementation. We have a unique setting in that we will repeatedly measure the changes in time demands on CHWs through the integration of ECD group sessions over a 12-month period. Measuring changes in CHW stress and psychosocial wellbeing over this period will provide some of the first quantitative evidence for the broader implications of a change in job responsibilities on health worker wellbeing.

#### Caregiver-child dyad participation

•*Primary Question 2: How does the integration of ECD activities affect participation by caregiver-child dyads in all activities led by CHWs?*•*Secondary Question 2: How is the treatment effect on caregiver-child dyad participation in health and nutrition activities moderated by key household and community characteristics?*

In addition to understanding time use among CHWs, this study also seeks to examine caregiver behavior and how the addition of ECD activities may affect participation of caregiver-child dyads. Attendance at the ECD sessions is likely to be time consuming, competing with caregivers’ productive activities and housework/caregiving duties, thereby negatively affecting take-up/participation of nutrition health activities. Conversely, the introduction of ECD group sessions may increase the caregivers’ potential interest and knowledge, because of its novelty and supportive nudges. Consequently, one could expect increased take-up of nutrition/health activities for existing caregiver-child dyads or new registration for health and nutrition programs of caregiver-child dyads who are in the community. The main outcome of interest will be an index of participation in the standard nutrition and maternal/child health activities. We will also examine how participation in the CHW-led activities may be affected by key household-level (e.g. maternal education), and community-level (e.g. remoteness) characteristics. A previous study found that there was some suggestive effects of heterogeneity of ECD outcomes by child age and maternal education [6]; measuring intermediate outcomes could be helpful in further understanding pathways in ECD.

#### Age-appropriate play materials

*• Primary Question 3: How does the availability of age-appropriate materials/activities for home-based play affect caregiver-child dyad participation in ECD activities?*

Toys, books and other age-appropriate play materials are crucial for young children to use in play because of the ways that these items promote engagement and promote learning. In addition to clear benefits of these items to promote children’s development, toys and books are also critical to sustain mothers’ interest in ECD activities by creating opportunities for home-based play. A recent meta-analysis including 13 RCTs showed medium-to-large benefits of stimulation interventions for improving the home caregiving environment, which includes having materials such as books and toys for children to play with [20]. A key component of our behavioral theory of change (the Integrated Behavioral Model) goes beyond motivation and knowledge and focuses on the idea that environmental constraints, such as a home without appropriate play materials, should not hinder the application of the new knowledge [21]. Another pillar of our design is that the behavior (developmentally-appropriate play and stimulation) should be salient to the individual, which is the reason we are focusing on the provision of toys, books and materials for participants to take home as a way to enhance engagement. Finally, we intend for the experience performing the behavior to become habitual so that true behavior change can occur and aim to promote habits with a combination of a toy box that is provided at home to each target child, as well as a rotating set of developmentally appropriate toys and books that participants can take home and use in between group sessions.

## Design

### Study setting

Our study will take place in 75 communities in two regions (Amoron’i Mania and Haute Matsiatra) out of four regions currently covered by the existing community-based health and nutrition program (Fig. 1). The region of Itasy was excluded from our sample frame due to an ongoing LNS supplementation program and Vakinankaratra was excluded due to weak institutional capacity in that region. The study population is composed of CHWs serving these communities at the time of randomization, and caregivers with children between 6 and 30 months of age.

**Fig. 1 Fig1:**
[figure not shown]
Map of districts in Madagascar. Note: Study will take place in the regions of Haute Matsiatra and Amoron i’Mania, excluding the districts of Ikalamavony and Ambatofinandrahana. The map was created by the authors using R (source of geodata shapefiles, administrative level 4: United Nations Office for the Coordination of Humanitarian Affairs (OCHA)).

### Eligibility criteria

Our sampling frame draws from the universe of communities participating in the national health and nutrition program as of September 2020 in the regions of Amoron’i Mania and Haute Matsiatra. Districts with extreme problems of accessibility (an issue for frequent monitoring) were ineligible and excluded (Fig. 2). From this universe of 1,185 potential communities in eight districts, the following inclusion criteria were used to select communities, for operational feasibility:•No other ECD programs present in the community or neighboring communities;•At least 40 children monitored at the nutrition center in the target age range of 6–30 months (monitored is defined as attending at least one growth monitoring session between July 2019 to August 2020);•Stable supervisory presence. Local NGOs are contracted to monitor and supervise all community health workers and help to strengthen linkages with local structures such as the community health committees and primary care facilities. Each NGO supervisor is in charge to up to 9 communities, which they visit twice a month. We defined stable presence as not having had NGO turnover within the last year.

**Fig. 2 Fig2:**
[figure not shown]
Flow of study implementation

### Recruitment

Local agents (the government Regional Nutrition Office and the local NGOs) will carry out the initial recruitment of communities by introducing the ECD curriculum structure and scope. At this time, CHWs (two per community) will indicate whether they would be willing to participate in a two-week training session and implement the ECD group sessions in their community for a one-year period and participate in monthly surveys. If a CHW declines to participate, a replacement community will be chosen. Informed consent for the administration of the survey will be collected by the local agents after this introduction to the planned activities and will be collected again more formally by the survey firm at baseline, after the training has occurred.

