### Sampling, stratification and randomization

In order to capture efficiency gains from adjusting from observable differences in the design of the randomized experiment, we conducted stratified sampling [28]. We partitioned the covariate space into 16 strata, with stratification criteria that included region (Amoron’i Mania and Haute Matsiatra), remoteness of the community (above/below the median Euclidean distance to the closest health center), population size of the catchment area (above/below median number of children in the 6–30 months old age range), and CHW education level (above/below secondary level of educational attainment).

Within each of the 16 strata, we sampled six or 12 communities (one sextuplet drawn from each of seven smaller strata and two sextuplets drawn from each of nine large strata) to create a set of 25 sextuplets that are comparable along the stratification dimensions. Next, we randomly drew three communities selected from each sextuplet and allocated each to one of three possible arms (i.e. allocation ration of 1:1:1 in two treatment arms and one control arm) for a total of 75 communities in the final sample. This sampling approach ensures that each community has a cluster of comparable communities within its assigned stratum and allows for up to three back up communities for the potential need for replacement in case of refusal or drop-out by participating communities [28, 29]. All sampling and randomization were done by key research personnel using standard and reproducible computer-assisted software packages in Stata 16.

The random generation sequence and the random assignment of (i) communities to treatment arms and of (ii) households in case of over-subscription in T and T + will be performed by the research team. Due to the nature of the interventions, it is impossible to blind participants to their intervention group assignment. Interviewers will not be blinded as they will ask participants about their program-related experiences. However, the data will be masked to group assignment during the data analysis phase to blind the data analysts.

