### Statistical methods for primary and secondary outcomes

#### General analytic approach

Primary analyses will be conducted on an intention-to-treat (ITT) basis.

Identification of causal impacts will rely on the random assignment of treatment at the community level. The main impact of the program activities will be measured through a series of pair-wise comparisons of mean outcomes between the study arms. However, it is possible that by chance alone we will find a covariate imbalance between communities in different treatment arms that could confound our estimates. Therefore, we will measure theoretically significant covariates at the caregiver-child dyad level, CHW and community levels to include in a regression framework.

The potential for contamination or spillover effects for CHWs and caregiver-child dyads across communities for the program is low, as communities are self-contained and provide services to mothers and children registered in the local community.

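### Allocated communities that refuse or drop out may be replaced by back-ups, and the plan does not reconcile this with ITT or with a population fixed at randomization

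*Protocol article*

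**What the plan says.** Under Sampling, stratification and randomization, the article builds 25 sextuplets and then reports: "Next, we randomly drew three communities selected from each sextuplet and allocated each to one of three possible arms". The undrawn half of each sextuplet serves as a reserve, because the approach "allows for up to three back up communities for the potential need for replacement in case of refusal or drop-out by participating communities".

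Under Recruitment, local agents introduce the ECD curriculum and "CHWs (two per community) will indicate whether they would be willing to participate in a two-week training session and implement the ECD group sessions", together with the monthly surveys. The rule that follows is: "If a CHW declines to participate, a replacement community will be chosen". Informed consent for the survey is taken at that introduction and "will be collected again more formally by the survey firm at baseline, after the training has occurred".

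Two other statements bear on this. General analytic approach says: "Primary analyses will be conducted on an intention-to-treat (ITT) basis". Study setting says: "The study population is composed of CHWs serving these communities at the time of randomization".

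**The concern.** ITT means that each randomized unit is analysed in the arm to which it was allocated. A back-up that enters after allocation was never drawn for an arm, and the community it replaces was. If the back-up takes over the place and the randomized community leaves the data, the comparison no longer rests on random assignment.

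The outcomes make this more than a formality. Primary Question 1 is CHW time use, Secondary Question 1 is CHW wellbeing, and Primary Question 2 is participation in activities led by the same CHWs. A community that drops out of an ECD arm may do so because of the added work, which control CHWs do not have. Replacement could then depend on arm and be related to these outcomes.

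**Working it through.** **1. Scale of the reserve.** Seven strata with one sextuplet and nine with two ("one sextuplet drawn from each of seven smaller strata and two sextuplets drawn from each of nine large strata") give 7 + 18 = 25 sextuplets. That is 25 × 6 = 150 communities sampled, 25 × 3 = 75 allocated and 75 held back. These figures agree with the article.

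**2. Order of events, by trigger.**
- *Drop-out by a participating community.* This can only follow allocation, so a replacement here is always post-allocation.
- *Refusal at first recruitment.* The willingness question goes to the two CHWs per community. No arm is named, and no timing relative to disclosure is given. The tenses do not settle it: the sampling section reports the draw and allocation as done, while the Abstract and part of the sampling section put assignment in the future.
- *Refusal at formal consent.* This comes after the training. Training is described under the ECD arm (Fidelity), so ECD CHWs probably know their arm by then. That is an inference, not a statement in the article.

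**3. How often a swap could occur (refusal rates assumed; the article gives none).** One refusal is enough, so with two CHWs the share of communities replaced is 1 − (1 − r)².
- r = 2%: 1 − 0.98² = 4.0%, about 2 of the 50 ECD communities
- r = 5%: 1 − 0.95² = 9.8%, about 5 of 50
- r = 10%: 1 − 0.90² = 19.0%, about 9 or 10 of 50

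**4. Illustrative shift if replacement acted in the ECD arms only.** Shift = share replaced × difference between replaced and replacing communities. With an assumed difference of 0.25 to 1 SD:
- 4% replaced: 0.04 × 0.25 = 0.01 to 0.04 × 1 = 0.04 SD
- 19% replaced: 0.19 × 0.25 = 0.05 to 0.19 × 1 = 0.19 SD

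Eq. 4 adjusts for the baseline outcome. If the article's autocorrelation of 0.5 to 0.7 is taken as the baseline slope, a stable difference shrinks by a factor of 0.5 to 0.3, so the upper figure becomes 0.19 × 0.3 = 0.06 to 0.19 × 0.5 = 0.10 SD. Differences in response to the ECD work would not shrink. If every community was asked before any arm was known, the shift from refusals is zero.

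**5. Is replacement needed for power?** Table 1 reproduces in all six cells. The formula is n per arm = 2 × ((1.96 + 0.84)/0.5)² × [(1 + 10ρ)/11 − ρ²], rounded up, then × (1 + ICC), rounded up. Two-sided alpha of 5% is assumed. For ρ = 0.5 and ICC = 0.3, n = 18.55, so 19, and 19 × 1.3 = 24.7, so 25. The formula counts CHWs, although the table is labelled clusters. Power at 0.5 SD for ρ = 0.5, ICC = 0.3 and k clusters per arm, if lost communities yield no data at all:

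| k | two CHWs per cluster | Table 1 read as clusters |
|---|---|---|
| 25 | 98.1% | 81.4% |
| 22 | 96.6% | 76.3% |
| 20 | 95.0% | 72.3% |
| 18 | 92.8% | 67.7% |

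Counting both CHWs, as planned, the trial can lose several communities per arm without needing substitutes.

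**The case against.** The strongest objection is that the article does not say that unwilling CHWs are screened out of the ECD arms only. A reader might infer that T and T+ are purged of overburdened CHWs while controls stay unselected, so that integration looks harmless. The documents do not support that reading. As written, the willingness question covers every recruited community. Asked of all before disclosure, it leaves the arms comparable and only narrows the population to which the results apply. This part of the objection stands.

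The direction of bias is open as well. Replacing communities that could not carry the load would make the time cost look smaller. But a community that stops ECD sessions and stays in the ITT set adds little ECD time, so replacing it with one that delivers them could make the cost look larger.

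It can also be said that back-ups are a contingency, that nothing removes a replaced community from the ITT set, and that an article may leave such detail to a fuller document. This stands in part: the article does not state an outright contradiction. But it does state a replacement provision that reaches past allocation, next to an ITT rule and a population fixed at randomization. These do not fit together as written.

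**Conclusion.** The point holds in limited form. The plan permits a randomized community to be replaced, after allocation, by one that was not drawn, and does not reconcile this with ITT or with the population defined at randomization. For drop-out this follows from the text alone. For refusal, the arm comparison is at risk only if CHWs know their arm when they decline.

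Neither size nor direction can be determined from the document. The shifts of 0.01 to 0.19 SD before baseline adjustment rest on assumed refusal rates, an assumed difference between communities, and replacement confined to the ECD arms. They show scale and are not an estimate. The gap should be closed because the rule can undo the randomization, and closing it costs little.

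**What to change.** - State the order of the willingness question, allocation, disclosure, training and formal consent. Define disclosure as the moment when a community first learns whether it is ECD or control, because the Treatment Plus section places the T+ allocation six months later.
- Allow replacement only before disclosure, after the same question has been put to all three communities of the triplet.
- After disclosure, replace no community in the primary analysis. Keep each one under its assigned arm. Use the CommCare records, which belong to program monitoring, for participation. Continue the CHW surveys where the CHWs consent; these are study data collection and do not continue by themselves.
- Report replacements by arm, with reason and date. For any already made, repeat the analysis without the affected triplets. This is a check and not a repair, because the remaining ECD communities are still those that stayed.

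The article says data collection is ongoing, so the analysis rule can still be set. The cost is wording and some extra follow-up. CHW survey data may be missing from those who refuse, and communities that do not deliver the sessions will dilute effects slightly.
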